**Figure 2 F2:**
[figure not shown]
Logic model for the Women’s Responses to Adjusted Product Placement and its Effects on Diet study. PPI, patient and public involvement. F&V, fruit and vegetables.

The control condition is the previous layout of stores with a limited range of fresh fruit and vegetables, placed at the back of the store. Both control and intervention stores will be sampled from locations across England to improve generalisability.

### Eligibility criteria

Participants will be women, aged 18–45 years, who hold a loyalty card with the study supermarket chain and have shopped in a study store in the 12 weeks before recruitment (according to loyalty card data). Shoppers who choose items in-store but opt for home delivery will be eligible. Women under the age of 18 or over 45 years, who do not hold a loyalty card or only shop online will not be eligible to participate.

### Participant recruitment

Women from matched intervention and control stores will be recruited in the same period prior to the intervention implementation stores’ refurbishment. Rolling recruitment over approximately 2 years will minimise bias from seasonal patterns of fruit and vegetable availability or consumption. Eligible women, identified from the loyalty card register, will be sent an invitation and information letter. Participants are not informed of the intervention. The letter invites them to participate in a study that is researching the food shopping and eating patterns of women aged 18–45 years. The letter will be sent by the supermarket to comply with data protection laws. Interested women will contact the study team via Freephone number, text or email; they will be screened for eligibility and consented. In-store recruitment will also be used, whereby members of the research team approach women customers while shopping and provide them with a study information sheet. Women will register their interest with the researcher in-store and are phoned at a suitable time for them to be consented. This method proved effective at enhancing representation of disadvantaged customers in a previous supermarket pricing trial.^26^ Both intervention and control participants will be recruited using these two methods which were identified as most successful during feasibility testing.

To ensure compliance with data protection laws, participants who have provided informed consent to the study team and completed the baseline survey will be sent an email from the collaborating supermarket to seek explicit consent for their loyalty card data, covering the 9-month study period, to be shared with the WRAPPED study team. Separate consent to take part in the process evaluation substudies will be obtained. Participants can withdraw from the study at any point without giving a reason and without affecting their relationship with the collaborating supermarket.

All participants will be offered up to £30 in Love2Shop vouchers as compensation for their time given to the study. Our patient and public involvement (PPI) representatives highlighted that vouchers would be preferable to financial payment which may interfere with benefit payments. Our incentive value is similar to an Australian supermarket pricing trial that used incentives equivalent to $A75 to optimise recruitment and retention.^27^ Distribution will entail 1x £10 Love2Shop voucher after completion of baseline, 3-month and 6-month questionnaires.

### Outcome measures

This study is unique in its collection of individual-level sales data, as well as demographic and dietary information, and is the first supermarket study to collect dietary data for more than one family member.^28^ Primary (purchasing) and secondary (store sales) outcome data will be obtained through the supermarket’s loyalty card scheme; other secondary outcome (dietary quality, fruit and vegetable intake) and demographic data will be collected via telephone surveys at baseline and 1, 3 and 6 months after intervention commencement. Using telephone interviews can overcome low-literacy levels and enhance participation of disadvantaged women.

#### Primary outcome

The primary outcome is change in participant’s weekly fruit and vegetable purchasing patterns from baseline (3 months prior to refurbishment) to the 3–6 months period postrefurbishment. Change in fruit and vegetable purchasing from baseline to the 0–3 months period postrefurbishment will also be assessed to measure short-term purchasing effects. These data will be obtained through the supermarket chain’s loyalty card scheme and provide information about the number of items for each product purchased at each store visit during the study period. We will also examine sales of frozen fruit and vegetables (for substitution effects). The research team will aggregate these data from each visit to a weekly structure for analysis to enable our data to be presented as items (bags of fruit/vegetables because these products are not sold singly at the collaborating supermarket chain) per household per week which is comparable to analyses conducted in previous supermarket trials.^27 29^

#### Secondary outcomes

The secondary outcomes include women’s and young children’s dietary quality, women’s daily fruit and vegetable intake, weekly store sales and economic analyses. Measures of women’s and their young children’s dietary quality will be assessed using published tools.^30 31^ Participants will be asked to indicate how often in the previous month they (or their child) consumed each of the 20 foods. A dietary quality score for each woman or child will be calculated by multiplying their reported frequency of consumption of each of the 20 items from their Food Frequency Questionnaire (FFQ) by corresponding weightings derived from the appropriate principal components analysis and then summing the results. Dietary scores will be standardised to have a mean of 0 and SD of 1. Higher diet scores represent better dietary quality characterised by higher intakes of vegetables, fruit, water and wholegrain bread and lower intakes of white bread, processed meats, fried/oven chips, crisps and sugar. Women’s daily fruit and vegetable intake will be measured via a two-item tool.^32^ We will assess change in daily portions of fruit and vegetables to quantify the independent effect of this aspect of diet; this measure details change in the amount (quantity) of fruit and vegetables eaten and will provide complementary data to the changes in frequency collected by the FFQ. Store sales data will be provided from electronic transaction records aggregated to the weekly level to enable comparison with previous work.^33^ Weekly store sales data will cover the periods from 3 months prior to refurbishment (baseline), and 0–3 and 3–6 months postrefurbishment. Data will cover the same retail weeks for each matched pair of stores to account for seasonal variation. The product categories created for the individual purchasing data will also be used for the store sales data.

### Economic evaluation

The economic evaluation will be conducted from three perspectives, individual, retailer and societal, and plans to estimate the costs and effects of the store refurbishment programme over 5, 10 and 20-year time horizons using scenario analyses. These long-term projections will require assumptions about the persistence of observed changes to shopping habits and dietary behaviour beyond the 6-month study follow-up. A range of possible scenarios will be assessed, with waning of effects over periods from 6 months to 20 years. Individual and retailer results will be presented as simple cost–consequence analysis tables, with estimates of monetary costs or savings shown in a ‘balance sheet’ alongside summary statistics for other relevant outcomes. Individual perspective evaluation will use participant survey data for food expenditure, time spent food shopping, fruit and vegetable waste as well as travel costs to and from supermarkets; these data will be supplemented by loyalty card data. Retailer perspective estimates will be generated through discussion with supermarket staff. These may include the cost and expected lifespan of the intervention, ongoing costs such as additional refrigerator storage, extra produce deliveries, produce waste, changes in product group sales (displacement, substitutions and complements) and staff costs. Results will be presented at an aggregated level to respect commercial confidentiality. The financial impact of changes in sales volumes will be estimated using publicly available information to reflect expected profit margins within the industry. Societal perspective evaluation will use a cost–utility analysis to assess the efficiency of the intervention investment in relation to future costs and savings to public and private bodies and health effects for the women, as well as the impact on health inequalities. Health effects and related treatment and care costs will be estimated using the published IMPACTNCD model, which simulates the incidence of diabetes, coronary heart disease and stroke for a synthetic population with defined demographic, socioeconomic and clinical risk factors.^34^ Future costs/savings and quality-adjusted life years will be discounted using rates recommended in the National Institute for Health and Care Excellence reference case for public health guidelines at the time of analysis: currently 3.5% per year for costs and health outcomes (3.5% for costs and 1.5% for health outcomes in scenario analysis).^35^

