## Ethics and dissemination

Ethical approval for the WRAPPED study has been
obtained from the University of Southampton, Faculty of Medicine Ethics
Committee (ID 20986.A4). This study will be conducted in accordance with the Declaration of Helsinki, Good Clinical Practice guidance, Research Governance Framework for Health and Social Care and Data Protection regulations. WRAPPED is registered with ClinicalTrials.gov (NCT03573973). An independent study steering committee will provide strategic guidance, monitor progress and assess professional conduct throughout the study duration. There is no data monitoring committee for this study because the risks to participants are minimal.

This intervention has the potential to improve the diets and health of women of childbearing age from disadvantaged backgrounds and provide cost savings to the NHS; even modest increases in fruit and vegetable intake (0.3–1.0 portion/day) could reduce risk of later coronary heart disease by 4% and stroke by 5%.^48 49^ Additionally, collecting primary and secondary outcome data at the individual level will provide greater understanding of which individuals are susceptible to healthier food placement interventions and offer valuable evidence for policy-makers. The study findings will be disseminated through multiple pathways to ensure wide-reaching distribution to local, national and international audiences. On completion of the trial, two manuscripts will describe the:(1) results in relation to the primary and secondary objectives and (2) process evaluation findings. We will develop a media strategy with our PPI members and retail collaborators to raise awareness of the role of supermarkets in promoting healthy food choices, produce policy briefings to inform government action and create guidance for academics and professionals, outlining successful methods for research partnerships with food retailers to help improve the quality of existing evidence.

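### The societal cost-utility analysis stops at 20 years for women aged 18–45, so later QALYs and care savings from events averted within the horizon are left out; a lifetime horizon should be added

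*Protocol article*

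**What the plan says.** The Economic evaluation section of the protocol article covers three perspectives (individual, retailer, societal) and "plans to estimate the costs and effects of the store refurbishment programme over 5, 10 and 20-year time horizons using scenario analyses". No longer horizon is named, and none of the three is called the base case.

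On persistence beyond the 6-month follow-up it says: "A range of possible scenarios will be assessed, with waning of effects over periods from 6 months to 20 years".

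The societal perspective is a cost–utility analysis covering "future costs and savings to public and private bodies and health effects for the women, as well as the impact on health inequalities". Health effects come from a published model "which simulates the incidence of diabetes, coronary heart disease and stroke for a synthetic population". Discounting is 3.5% a year for costs and health, with a scenario of 3.5% for costs and 1.5% for health.

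Under Eligibility criteria, "Participants will be women, aged 18–45 years". Under Ethics and dissemination, a modest rise in fruit and vegetable intake is said to be one that "could reduce risk of later coronary heart disease by 4% and stroke by 5" per cent. The protocol thus itself places the benefit later in life.

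**The concern.** Two time spans need to be kept apart: how long the intervention changes behaviour, and how long the consequences of that change are counted. The plan varies the first from 6 months to 20 years and caps the second at 20 years. The effect that lasts longest therefore ends exactly when the longest model closes.

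A stroke averted in year 15 goes on yielding QALYs and saved care costs after year 20, whether or not the shopping effect has ended by then. Every stated horizon cuts these off. The population is young and the modelled diseases become more common with age, so the part cut off may be large.

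The study is meant to inform government policy. A societal result that leaves out later gains could make the layout change look poorer value than the same effect estimate would support over a lifetime.

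**Working it through.** The documents give no cost per QALY, QALY gain, incidence or cost amount, so there is no stated figure to reproduce.

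**Step 1. Age at cut-off** (entry age plus horizon, from the eligibility ages and stated horizons)
- 5 years: 18 + 5 = 23 to 45 + 5 = 50
- 10 years: 28 to 55
- 20 years: 38 to 65

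**Step 2. One averted event.** Assume an event averted in year 15 in a woman aged 40 at entry, with a constant yearly gain to age 85 (year 45), discounted at 3.5%. The share counted by year 20 is

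(1.035^−15 − 1.035^−20) / (1.035^−15 − 1.035^−45) = (0.597 − 0.503) / (0.597 − 0.213) ≈ 0.25.

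About three quarters of the gain from that event is dropped.

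**Step 3. All ages and event times, simple model.** Assumptions not in the documents: ages uniform over 18–45; event risk proportional to 2^((age + t − 50)/d) with d = 6, 8, 10 or 12 years; effect max(0, 1 − t/w), where w is the waning period; constant gain from each averted event to age 85. The share captured at horizon H is the discounted gain up to H divided by the discounted gain to age 85. Results at 3.5%, in fine time steps:

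| Waning period w | H = 5 | H = 10 | H = 20 |
|---|---|---|---|
| 6 months | 19% | 35–36% | 61–62% |
| 5 years | 13% | 31% | 58–59% |
| 10 years | 8% | 25% | 55% |
| 20 years | 3–4% | 12–15% | 43–46% |

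With health discounted at 1.5%, the 20-year column spans 34–51%.

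**Step 4. A different model structure.** A healthy/diseased/dead cohort run to age 100. Assumptions not in the documents: incidence 0.3% a year at age 50, doubling every 6, 8 or 10 years of age; Gompertz mortality, doubled after an event; utility loss and case fatality each 0.1 or 0.3; lag of 0 or 5 years. From the documents: a 4% risk reduction, both discount rates, and persistence of 6 months to 20 years.
- 5 and 10 years: at most 23% and 43% of the lifetime gain in any run (entry ages 18, 31.5 and 45).
- 20 years, entry age 31.5, 3.5%: 24–45% with 20-year linear waning; 43–63% with 6-month waning.
- 20 years, extremes of age at 3.5%: 21–40% at entry age 18 with 20-year linear waning; 48–74% at entry age 45 with 6-month waning.
- If the effect stays full for 20 years and then stops, the 20-year share at age 31.5 is 14–34%.

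**Step 5. What this does to the ratio.** For a positive net cost, cost per QALY at H relative to lifetime = (share of cost inside H) / (share of QALYs inside H). Take H = 20, entry age 31.5 and 3.5%.
- All cost up front, 20-year waning: 1/0.45 ≈ 2.2 to 1/0.24 ≈ 4.
- Level annual cost for 50 years: cost share (1 − 1.035^−20)/(1 − 1.035^−50) ≈ 0.61. The ratio is 0.61/0.45 ≈ 1.3 to 0.61/0.24 ≈ 2.5.
- Same cost stream, 6-month waning, highest share: 0.61/0.63 ≈ 0.97, so no overstatement.

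**The case against.** The strongest reply is that this is a declared set of scenarios and not an error. The horizons serve all three perspectives, and a lifetime horizon has little meaning for the retailer. Only 6 months of behaviour are observed, and every further year adds modelled content. This stands as a reason to keep the 5, 10 and 20-year results and to limit the change to the societal analysis. It does not justify the cut-off, because a lifetime horizon leaves the assumed persistence of the shopping effect unchanged.

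A reader might infer more than the documents support:

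- *That most of the gain is lost even at 20 years.* Not established. In the simple model at 3.5%, more than half is captured when waning takes 10 years or less. Only 20-year waning falls below half.
- *That the cost per QALY is overstated as a matter of fact, by a known multiple.* The documents give no costs or incidence, so every multiple above is an assumption. The article also hopes for NHS savings. If the intervention saves money overall, the fault is an understated gain and there is no positive ratio to inflate.
- *That the investment falls early and is counted in full, so the bias can run only one way.* The Economic evaluation section also lists the intervention's expected lifespan and continuing costs such as storage, deliveries, waste and staff, without timing. Step 5 shows a case where the overstatement disappears.
- *That nobody over 65 can enter the model.* Age 65 follows from the eligibility ages. The age structure of the model's synthetic population is not stated.

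**Conclusion.** The concern holds in a limited form. With horizons of 5, 10 and 20 years for women aged 18–45, the societal analysis omits QALYs and care savings that follow the cut-off from events averted before it, and the waning scenarios do not restore them. Less than half of the discounted lifetime health gain is captured at 5 and 10 years under every assumption tried. At 20 years the share is roughly 25–60% for central assumptions and wider at the extremes of age, waning shape and discount rate.

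The likely result is understated QALYs and treatment savings. Where net cost is positive and not mainly incurred after the horizon, the cost per QALY is likely to be overstated. Direction and size both rest on incidence, survival and cost assumptions from outside the documents. The point concerns one secondary objective and leaves the effectiveness results untouched. It is a cheap improvement.

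**What to change.** In the Economic evaluation section, for the societal cost-utility analysis only:

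1. Add a lifetime horizon for the women, with the same waning scenarios (6 months to 20 years) and the same discount rates.
2. Report it alongside the 5, 10 and 20-year results.
3. Count continuing intervention costs over the same period as the health gains, so that numerator and denominator match.
4. State that the shorter horizons omit later gains and savings from events averted within them.

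The individual and retailer analyses can stay as planned. The cost is longer model runs and a few sentences of text; no new data are needed. The downside is more reliance on modelled survival and disease course at older ages, which reporting the horizons side by side makes visible.

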
### Sample size calculations

The study will be powered to detect differences in the primary outcome (fresh fruit and vegetable purchasing) between women in the intervention and control groups during the 3–6 months postintervention period. We used data from our previous research on women in Hampshire who were the same age range as the proposed participants of this study^15^ and considered the supermarkets at which the women shopped as clusters to estimate an r of 0.1 as our intraclass correlation coefficient. We aim to detect a difference of 0.3 item/average bag of fruit/vegetables (1.5 portions) per week. Assuming an SD of 0.7 item (3.5 portions) per week as seen in the pilot data, 16 stores in each arm and 30 women per store provides 90% power at a 5% significance level (two sided).

The study will also be powered to assess the secondary outcome of women’s dietary quality. Our previous research provided a rho of 0.1 as our intraclass correlation coefficient and a correlation coefficient of 0.8 for the means of women’s dietary quality at the store level between baseline and 2-year follow-up. Taking account of the clustering, and using the method of Teerenstra *et al*
36 to adjust for the method of analysis planned (adjusting diet quality score for baseline in the analyses), 16 stores in each arm with 30 women per store provides 85% power at a 5% significance level (two sided) to detect a difference in the diet quality scores at follow-up of 0.23 SD. Additionally, assuming that half the women have children aged 2–6 years, 16 stores in each arm will also provide 80% power to detect a difference in the children’s diet quality scores of 0.25 SD using the methods described above. Having fewer participants but retaining the full number of clusters has relatively little impact on the anticipated power.^37^ The recruitment plan will oversample with 18 stores in each arm to account for potential store closure and up to 45 women per store to account for attrition.

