### Statistical analysis

We will conduct analyses involving three-level multilevel models, with women’s weekly purchasing data clustered within women, who are clustered within stores. Weekly purchasing data are not normally distributed and therefore an alternative continuous distribution such as the negative binomial distribution will be considered or a binary variable will be used. With the data in ‘long’ format, an interaction between intervention group and time period will indicate whether there is a difference in change in sales from the 3-month baseline period to the 0–3 months and 3–6 months periods postintervention between the control and intervention stores. These models will be adjusted for sales from the 3-month baseline period as an efficient analysis of the changes in purchasing taking account of regression to the mean.^38^

Effect modification by educational level will be assessed by including a multiplicative interaction between intervention group and education level in the individual purchasing models. If there is evidence of an interaction, stratified analyses will be performed to determine the strength and direction of intervention effects for each level of educational attainment.

Women’s dietary quality scores (SD) will be calculated at baseline, 3 and 6 months. Multilevel linear regression models (with women clustered within stores) will be used with dietary quality score as the outcome measure, intervention group as the exposure and baseline diet scores included in the model to account for regression to the mean.^38^ Confounders will be determined by a directed acyclic graph.^39^ Analyses of other secondary outcomes (ie, daily fruit and vegetable intake and child’s dietary quality) will adopt the same statistical approach as that for women’s dietary quality.

Store sales data will be analysed using multilevel models to account for the clustering of weeks within stores. Weekly sales data will be the outcome and will be transformed to normality using Fisher-Yates transformations.^40^ Analyses will use interrupted time series models^41^ with CIs calculated at the 3 and 6 months postintervention commencement time points using the delta method.^42^ Statistical analyses will be conducted in Stata.^43^

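### The 85% power for women's diet quality uses the correlation of store means, but the model as described names no store-mean baseline term; adding one would make the analysis match the power calculation

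*Protocol article*

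**What the plan says.** All references are to the protocol article.

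- **Sample size calculations, women's diet quality.** The design is "16 stores in each arm with 30 women per store", powered at 85% (two-sided 5%) "to detect a difference in the diet quality scores at follow-up of 0.23 SD". The clustering input is stated as "Our previous research provided a rho of 0.1 as our intraclass correlation coefficient". The baseline input is "a correlation coefficient of 0.8 for the means of" women's diet quality, taken at store level between baseline and a 2-year follow-up. The calculation is said to reflect the planned analysis, described as "adjusting diet quality score for baseline in the analyses".
- **Secondary outcomes.** "Dietary scores will be standardised to have a mean of 0 and SD of 1", so effects are in SD units.
- **Statistical analysis.** The women's diet model is a linear multilevel model with women nested in stores, and with "baseline diet scores included in the model to account for regression to the mean". Further covariates are left to a directed acyclic graph. The child diet and fruit and vegetable intake analyses follow the same approach.
- **Study setting.** Stores are not randomised. Controls are matched on sales profile, customer profile and deprivation.

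The article gives no baseline-to-follow-up correlation for individual women. It neither mentions nor excludes a store-mean baseline term.

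**The concern.** The power calculation and the described model appear to use the baseline at different levels. The calculation takes its variance reduction from how well a store's baseline mean predicts its follow-up mean. A model with one coefficient on each woman's own score estimates that coefficient mostly from differences between women in the same store, because with 30 women per store most of the information lies there. That slope need not equal the store-level slope. A store mean averages out individual reporting error and short-term variation, so an individual slope below 0.8 is plausible, although the article does not report it.

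Two things are at stake. The first is precision: if the slopes differ, the model does not obtain the full reduction behind the 85%. The second is adjustment: with non-randomised stores, the arms may differ in baseline store means, and a slope that is too shallow corrects only part of that difference.

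**Working it through.** **Inputs from the article:** 16 stores per arm, 30 women per store, intraclass correlation 0.1, store-mean correlation r = 0.8, difference 0.23 SD, SD 1, two-sided 5%. **Not in the article:** the within-store slope b, assumed here to lie between 0.4 and 0.8. Equal variances at baseline and follow-up are assumed, so slopes and correlations are on the same scale.

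**Step 1. Reproduce the stated power.**
- Design effect: 1 + 29 × 0.1 = 3.9.
- Variance factor from baseline adjustment: 1 − 0.8² = 0.36.
- SE = √(2 × 3.9/480 × 0.36) = √0.00585 = 0.0765.
- 0.23/0.0765 = 3.01, which gives 85.2% by the normal approximation (82.8% using t with 29 df).

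The stated 85% is reproduced. With no baseline adjustment, power would be 43.8%, so the 0.36 factor matters a great deal.

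**Step 2. Replace the factor for a single individual-level slope.** If the model subtracts b times each woman's own baseline, the store-mean variance relative to the unadjusted one is

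1 − 2b(0.8) + b² = 1 − 1.6b + b².

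This equals 0.36 only at b = 0.8.

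| b | Factor | Power (normal) | Stores per arm for the same precision (16 × factor/0.36) |
|---|---|---|---|
| 0.8 | 0.36 | 85.2% | 16 |
| 0.7 | 0.37 | 84.3% | 16.4 |
| 0.6 | 0.40 | 81.4% | 17.8 |
| 0.5 | 0.45 | 76.7% | 20 |
| 0.4 | 0.52 | 70.6% | 23.1 |

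**Step 3. Are these values of b compatible with r = 0.8?** The store-mean variance is 0.1 + 0.9/30 = 0.13. Setting (0.1 × c + 0.03 × b)/0.13 = 0.8, where c is the correlation of the true store effects, gives c = 0.80 at b = 0.8, 0.89 at b = 0.5 and 0.92 at b = 0.4. All are possible, so the stated inputs do not determine b.

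**Step 4. Check by simulation.** Random-intercept models were fitted to 2,000 simulated trials per scenario, with a z test.

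| b | Mean fitted slope, individual baseline only | Power, individual baseline only | Power, store mean added |
|---|---|---|---|
| 0.8 | 0.80 | 85% | 84% |
| 0.7 | 0.70 | 84% | 84% |
| 0.6 | 0.61 | 81% | 83% |
| 0.5 | 0.52 | 76% | 83% |
| 0.4 | 0.42 | 70% | 82% |

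The fitted slope follows the within-store value, as the formula assumes.

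**Step 5. Unadjusted store-level imbalance.** Relative to adjustment at the store-level slope, the part left over is about (0.8 − b) × the observed arm difference in baseline store means. Under chance alone that difference has SD √(2 × 3.9/480) = 0.1275. A one-SD imbalance therefore leaves 0.3 × 0.1275 = 0.038 SD at b = 0.5, 0.2 × 0.1275 = 0.025 SD at b = 0.6, and nothing at b = 0.8, against a target of 0.23 SD.

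**Step 6. Child diet.** Taking 15 children per store (half of 30), the same intraclass correlation and the same r = 0.8, which the article implies by using the same methods, the design effect is 2.4. For 0.25 SD, power is 83.8% at factor 0.36 and about 75% at factor 0.45 (b = 0.5). The article states 80%.

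**The case against.** **The article does not say that only the woman's own baseline is used.** This stands. The individual-only reading is the natural one, but it is inferred from a condensed text whose analysis plan is not shown. A reader might infer that the protocol rules out store-level adjustment; it does not.

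**Nothing stated is wrong, and the loss may be negligible.** This also stands. A reader might infer that the 85% is miscalculated or that the comparison is underpowered. The documents support neither: the figure reproduces, b is not given, and the loss is nil at 0.8, about 1 point at 0.7 and about 4 at 0.6.

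**The 0.8 comes from a 2-year interval, while the trial follows women for 3 and 6 months, so r could be higher.** With an assumed r = 0.9 and b = 0.5, the factor is 1 − 0.9 + 0.25 = 0.35, giving 86% with the individual baseline alone. So the statement that power needs b near 0.8 is true only with r held at 0.8. But in that same case the store-mean term would bring the factor down to 1 − 0.81 = 0.19, so a higher r strengthens the case for including it.

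**The plan recruits 18 stores per arm.** If none closed, power would be about 86% at b = 0.6 and 81% at b = 0.5. Those stores are held against closures, however, and extra stores do not correct a baseline imbalance.

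**Matching and chosen confounders may already reduce imbalance.** They may, but the named matching factors do not include diet quality. A large bias is tempting to claim: an assumed 0.2 SD imbalance would leave 0.06 SD at b = 0.5. The article reports no imbalance of that or any size, and treating 0.8 as the right slope for arm differences is itself an assumption in a non-randomised design.

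**The extension to other outcomes.** No power is claimed for intake, and the child figure has some margin over its stated 80%. For those outcomes the argument is mainly about consistency and imbalance.

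**Conclusion.** The point holds as a cheap improvement to a secondary-outcome analysis. The 85% is arithmetically sound but conditional: if each woman's own score is the only baseline term, and r is 0.8, it is reached only when the within-store slope is close to 0.8. The shortfall is about 1 point at b = 0.7, 4 at 0.6 and 9 at 0.5. In the same circumstances, part of any store-level baseline difference between the arms stays uncorrected. The conclusion rests on reading the baseline term as individual-level, on an assumed range for b, and on equal variances at the two times. It does not show that the study is underpowered or that a biased estimate is to be expected.

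**What to change.** State whether the store mean of the baseline score is a covariate. If it is not, add it beside the individual baseline score in the women's diet model and in the child diet and intake models that follow the same approach. Separate within-store and between-store baseline terms are equivalent. The analysis then uses the correlation on which the power calculation depends, and the variance factor returns to about 0.36 whatever b is.

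The cost is one store-level degree of freedom and no new data. In the simulations this was at most about 1 point of power (at b = 0.8). The gain was about 7 points at b = 0.5, with little or none at 0.7 or above.
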